# Efficacy of conditioned autologous serum therapy (Orthokine®) on the dorsal root ganglion in patients with chronic radiculalgia: study protocol for a prospective randomized placebo-controlled double-blind clinical trial (RADISAC trial)

**DOI:** 10.1186/s13063-023-07787-y

**Published:** 2023-11-25

**Keywords:** Lower limb radiculalgia, Pulsed radiofrequency, Dorsal root ganglion, Autologous conditioned serum

## Abstract

**Background:**

Pulsed radiofrequency (PRF) treatment on the dorsal root ganglion (DRG) has been proposed as a good option for the treatment of persistent radicular pain based on its effect of neuromodulation on neuropathic pain. Autologous conditioned serum (ACS) therapy is a conservative treatment based on the patient’s own blood. The aim of this manuscript is to develop a study protocol using ACS on the DRG as a target for its molecular modulation.

**Methods:**

We plan to conduct a randomized controlled study to compare the efficacy of PRF therapy plus ACS versus PRF therapy plus physiological saline 0.9% (PhS) on the DRG to reduce neuropathic pain in patients with persistent lower limb radiculalgia (LLR) and to contribute to the functional improvement and quality of life of these patients.

Study participants will include patients who meet study the inclusion/exclusion criteria. Eligible patients will be randomized in a 1:1 ratio to one of treatment with PRF plus ACS (experimental group) or PRF plus PhS (placebo group). The study group will consist of 70 patients (35 per group) who have experienced radicular pain symptoms for ≥ 6 months’ duration who have failed to respond to any therapy. Both groups will receive PRF on the DRG treatment before the injection of the sample (control or placebo). Patient assessments will occur at baseline, 1 month, 3 months, 6 months, and 12 months after therapy.

The primary efficacy outcome measure is Numeric Pain Rating Scale (NPRS) responders from baseline to 12 months of follow-up using validated minimal important change (MIC) thresholds. A reduction of ≥ 2 points in NPRS is considered a clinically significant pain relief.

The secondary efficacy outcome measure is the proportion of Oswestry Low Back Pain Disability Scale (ODS) responders from baseline to 12 months of follow-up in the experimental group (PRF plus ACS) versus the placebo group (PRF plus PhS). ODS responders are defined as those patients achieving the validated MIC of ≥ 10-point improvement in ODS from baseline to 12 months of follow-up as a clinically significant efficacy threshold.

**Discussion:**

This prospective, double-blind, randomized placebo-controlled study will provide level I evidence of the safety and effectiveness of ACS on neuropathic symptoms in LLR patients.

**Trial registration {2a}{2b}:**

EUDRACT number: 2021–005124-38. Validation date: 13 November 2021. Protocol version {3}: This manuscript presents the 2nd protocol version.

**Supplementary Information:**

The online version contains supplementary material available at 10.1186/s13063-023-07787-y.

## Introduction {6a}

Radicular pain is defined as pain perceived in an extremity or trunk wall caused by the activation of nociceptive afferent fibers from a spinal nerve (International Association for the Study of Pain, IASP) [1]. Due to the physiology of neuropathic pain itself, radicular pain is related to lesions that directly compromise the dorsal root ganglion (DRG) or directly compromise the spinal nerve and its roots by causing ischemia or inflammation of the axons [2, 3].

Lower limb radiculalgia (LLR) has an annual prevalence in the general population of 9.9% to 25%, which means that radicular pain is probably the most common form of neuropathic pain [4, 5]. LLR fully or partially resolves in 60% of patients within 12 weeks of symptom onset. However, in 20 to 30% of patients, the pain persists beyond 3 months and even beyond 12 months, and when this occurs, the prognosis is usually already unfavorable. In addition, the repercussion of neuropathic pain at the personal, social, and economic level of these patients is well known in the current literature. For all these reasons, it should not be underestimated that when it becomes chronic, neuropathic pain ceases to be a symptom and then becomes a disease [6–8].

Despite the availability of many treatments for LLR, the currently available evidence is insufficient for optimal therapy [9]. Conservative treatment of radicular pain combines pharmacological management with physiotherapy [10–14]. Interventional techniques with epidural steroid injections and surgery are then reserved for patients’ refractory to conservative treatment [11, 15], but some of them are unsuccessful.

The persistence of pain requires a neuro-histological and neuro-molecular consideration in order to find the adequate treatment targets. This is the reason why DRG is focused as a target for neuromodulation. DRG plays a key role in developing and maintaining radicular pain and its link to sensory disturbances. Apart from the neuron’s electrical potentials, the glia will drive an immune cascade of inflammatory mediators leading to peripheral and central sensitization. In addition, the hyperexcitability in afferent fibers is associated with changes in gene expression, in the ion channels themselves, leading to discharges, spontaneous bursts, which are the electrophysiological signature of neuropathic pain [16–18].

PRF therapy on the DRG has been proposed as a good option for the treatment of persistent radicular pain based on its power of neuromodulation on neuropathic pain [16, 19–30]. It is also minimally invasive, inexpensive, and simple to perform with few complications. The effect of PRF on neuropathic pain resides through different mechanisms, including the generation of heat and an electric field that induces changes in DRG neurons [30]. More than 120 articles dating back 15 years in terms of DRG PRFs are available in the current literature, giving in its best results an improvement of 29.5% at 2 months, and in 13.1% of the patients who improved, this improvement lasted up to 50% still at 12 months [27].

In order to be able to offer effective treatments for LLR, it is necessary open the field of research towards the cellular and molecular changes induced on the DRG. ACS therapy is a conservative treatment based on the patient’s own blood. A simple sample is taken from the patient, incubated and separated using a special device to produce a serum that is high in anti-inflammatory cytokines and growth factors. This serum is injected back into the patient in a series of 2 to 3 doses.

Described in multiple clinical trials, ACS therapy reduces pain and improves function, mobility, and quality of life. Patients are treated safely without too many clinically relevant side effects. None of their rival treatments such as corticosteroid, hyaluronic acid, or platelet recombinant plasma (PRP) are unrivaled in terms of the duration of their effectiveness in reducing pain [31–37]. When studying the pathophysiology at the molecular level, it is estimated that cytokines play a fundamental role in inflammatory processes, in the pathogenesis of joint degeneration, in spinal pathologies, in soft tissue degeneration, and in the immune system, being a factor in this key interleukin-1 [33–35, 38]. If, therefore, all these molecules are used in combination with natural concentration and autologous, better therapeutic effects can be obtained than exogenous drugs.

For all these reasons, in this study, it is proposed not only to treat patients with radicular pain from a neuromodulatory therapy with PRF but also to add an autologous molecular therapy for the optimization and duration of the clinical improvement of neuropathic radicular pain. In this way, it is intended to treat the DRG electromagnetically and neurochemically in order to achieve the modulation and total reversal of the neuronal malfunction that comprises neuropathic pain {6b}.

### Study design

#### Objectives {7}

The primary objective of the RADISAC study is to measure the effectiveness of the PRF therapy plus ACS on the DRG neuropathic pain in patients with persistent LLR.

The secondary objective is to evaluate the functionality, the quality of life, and the mood of patients during the first year after the treatment.

## Methods

This is a prospective, double-blind, randomized placebo-controlled trial designed to assess whether therapy with PRF + ACS on the DRG compared to PRF + PhS reduces neuropathic pain and its consequences, in patients with persistent LLR {8}.

In addition, this it to evaluate if the fact of adding ACS can give a greater advantage for the reduction of pain in these patients.

Taking into account that pulsed RDF is currently the interventional treatment with the best results to offer to patients with persistent chronic radiculalgia, it is the design of the study proposed to perform PRF therapy on the DRG for 8 min, 45 V of the root affected to all the patients included in the study. At the end of the PRF therapy, a 3-mL dose of ACS will be administered on the DRG to the patients of the experimental group and a 3-mL dose of 0.9% PhS will be administrated on the DRG to patients of the placebo group.

A schematic patient flow diagram is presented in Fig. 1 as recommended by SPIRIT [39].

**Fig. 1 Fig1:**
[figure not shown]
Study patient flow

### Setting {9}

The project will be carried out in the facilities of the pain unit of Department of Anaesthesiology, Resuscitation and Pain Treatment at the Dexeus University Hospital (DUH) in Barcelona. The principal investigator is the first responsible of all the project and its development.

### Study population {10}

The study population proposed is 70 patients over 18 years of age, not illiterate, with radicular pain in the lower limb for more than 6 months. In addition, the symptomatic diagnosis screening criteria to confirm LLR will be used prior to the patient enrolment in the study. The inclusion and exclusion criteria are shown in Table 1.

**Table 1 Tab1:**
[figure not shown]
Inclusion and exclusion criteria

### Recruitment and informed consent

Both the main investigator and the other doctors of the pain unit will proceed to recruit patients within their usual clinical practice and according to inclusion and exclusion criteria {15}.

All the candidates will be informed in detail of the following information: the purpose of the study, interventions, benefits, possible risks, and corresponding responses. The patient accepts by signing the informed consent (IC) that he/she voluntarily participates in the study accepting that he/she may belong to the placebo or experimental group. They will sign the informed consent form voluntarily and will have the right to withdraw from the study at any time without any risk. The IC also includes a specific section on privacy consent and protection of personal data, according to the legal framework {26a} {26b} {6b}.

### Randomization {16a} {16b} {16c}

Randomization will be carried out using a simple randomization based on an equiprobable algorithm. According to randomization algorithm, a three-digit numerical code list will be generated with the R statistical software. It contains the three-digit and the assignation group. This list will be given to the laboratory and to the pharmacy service of the DUH, so only these both will know which of the groups is placebo and which of the groups is experimental. Only the part of the lists containing the 70 three-digit numerical code (not the assignation group) will be given to the main investigator. For each recruited patient, the main investigator will assign consecutively a three-digit code number and give to the patient a document with his name and the three-digit numerical code. When the patient will go to the laboratory, it will know if the patient belongs to the experimental group or the placebo group and proceed to prepare the samples. The principal investigator and the patients will be blinded for the remaining.

### Trial intervention and blinding {11a} {17a}

To comply with double-blind blinding, the following steps will be followed for the extraction and preparation of the ACS:

All patients will be scheduled 4 days before infiltration in the laboratory for blood collection and sample processing. Prior to extraction, patients will undergo the determinations based on the following documents: AEMPS REPORT/V1/23052013 and ROYAL DECREE 1088/2005. Given the laboratory will already know if the patient belongs to the experimental or placebo group, it will proceed to draw blood for the preparation of the ACS or not and store the syringes in the refrigerator at a temperature not exceeding – 18 °C.

All patients will undergo a blood draw for the preparation, or not, of the ACS, so they will not be able to know at any time which group they belong to. The syringes with the ACS or PhS samples are identical and sealed so that the main investigator will not be able to know to which group the patient belongs to. In addition, the way to evaluate the improvement or not of the pain will be through the self-assessment tests that the patient will answer individually at the control visits with what the main investigator will transcribe the results of the tests to the study database.

The day scheduled for infiltration, before performing the technique, adequate positioning of the patient, and proper monitoring in accordance with the protocol of the pain unit is mandatory. To perform the procedure, a transforaminal DRG approach technique will be performed under asepsis and antisepsis and under fluoroscopic vision. After checking the impedances (not higher than 450 ohms), the presence of sensory stimulation will be checked with a stimulation between 0.3 and 0.6 V and motor stimulation with a voltage at most double that is necessary to cause paresthesia. Finally, and once the injection of contrast is verified, PRF therapy will be carried out on the DRG (8 min, 45 V). Once the therapy is finished, the sample assigned to the patient will be injected.

Since most studies and clinical trials describe ACS therapy with 2 or 3 injections [31–37], separated in time by 7–15 days, the exact same procedure will be repeated 14 days after the first treatment.

Time schedule of enrolment, interventions, assessments, and visits for participants is shown in Table 2 (timeline) and Table 3 {13}.

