### Monitoring, safety, and quality control

The primary safety endpoint is the incidence of device- and/or procedure-related adverse events, which will be compared statistically between the randomized groups using proportions of patients experiencing such an event. The endpoint will be met if this event rate is not significantly greater with ACS than with PhS. All study-related adverse events will be monitored and reported, including seriousness, severity, treatment, and relationship to the study device/procedure. Adverse events collected in this study will be determined by the mine investigator to be specifically related to the products or procedures used in the 2 treatment groups or one that is determined to be a serious adverse event {22}.

To date, all published studies with ACS have shown high safety rates and no side effects for what ACS product itself represents. Even so, any intervention can lead to an adverse effect, so their monitoring will be an essential condition in this protocol {11b}.

Once the study has started, given that the inclusion of patients will be progressive over time as they are recruited, just in case there is a worsening of pain of more than 25% in more than 50% of the patients, the study would be reconsidered and the recruitment would be stopped to analyze the data and check if the worsening is in patients whom the ACS therapy was applied. If this were the case, the study would be definitively stopped and a report would be given to the laboratory. The author responsible for the study will carry out this audit if necessary. The main investigator together with the rest of the authors will make the decision to terminate the trial early {17b} {21a}.

Any other adverse effect as far as the interventions are concerned will be collected and analyzed (if necessary, the second intervention would be canceled, and the patient would be withdrawn from the study) {11b} {21b}.

The main investigator is the only person who will be in charge of follow-up with clinical interviews at 30 days, 3 months, 6 months, and 12 months. A schedule of visits will be established for each patient for their greater adherence to the study and not to delay follow-up. Apart from the following-up visit controls, the patients will provide from a telephone number of pain unit for any doubts, changing pain characteristics, or new interventions they will receive. In that way, it provides an improving of adherence to protocol of the study {11c}.

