As far as the samples are concerned, both the laboratory responsible for the ACS and the pharmacy of DUH will have a record of the samples and their transport and temperature. Each sample will have a special label (study code, randomization number) and will be guarded by the pharmacy upon arrival from the laboratory and when it is withdrawn by the investigator on the day of its use for injection.

The study will be carried out in the facilities of the DUH, a document of suitability of the facilities signed by the head of the Department of Anaesthesiology and pain unit. In the same way, a commitment document is attached by the Hospital’s Pharmacy Department for the control and monitoring of the study. The main investigator will take the responsibility to monitoring of the study. She will coordinate with the people in the laboratory, pharmacy, and pain unit. There is also a thesis director who will meet monthly with the author responsible for the study and running the trial day-to-day to provide organizational support. In conclusion, since the day-to-day task falls on the main investigator, she will be responsible for any important protocol modification and technical aspects of the trial as well as data collection, outcome analyses, and results. She will be in charge of notifying the rest of authors as well as laboratory and pharmacy {5d} {21a} {25}.

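### The main investigator's blind rests on matching sealed syringes, but nothing stated masks the serum or saline inside once they are opened and injected

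*Protocol article*

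**What the plan says.** **Trial intervention and blinding {11a} {17a}.** The main investigator's blind is explained by the syringes: "The syringes with the ACS or PhS samples are identical and sealed so that the main investigator will not be able to know" which group a patient is in. A second element follows at once. Improvement in pain is to be judged through "the self-assessment tests that the patient will answer individually at the control visits with what the main investigator will transcribe the results" to the database. The person who injects is not identified: "the sample assigned to the patient will be injected". The whole procedure is repeated after 14 days.

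**Methods.** On the contents: "a 3-mL dose of ACS will be administered on the DRG to the patients of the experimental group", and the other arm receives the same volume of 0.9% saline. The Introduction describes the serum as prepared from the patient's own blood.

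**Monitoring, safety, and quality control.** The labelled sample is in the pharmacy's care from its arrival, including "when it is withdrawn by the investigator on the day of its use for injection". On follow-up: "The main investigator is the only person who will be in charge of follow-up with clinical interviews at 30 days", and likewise at 3, 6 and 12 months. On safety: "Adverse events collected in this study will be determined by the mine investigator to be specifically related to the products or procedures" of the two arms, or to be serious (I read the fourth-last role word, an evident misprint, as main). The primary safety endpoint compares between arms the proportion of patients with a device- or procedure-related event. The same section gives the main investigator responsibility for collecting the data and analysing the outcomes.

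**Randomization and Data collection.** Only the laboratory and the pharmacy hold the allocation list. A researcher who is blind to allocation audits the spreadsheet every month.

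**The concern.** The article draws a conclusion (the main investigator cannot know the arm) from a premise about packaging. A seal protects the blind while the syringe is stored and carried. It stops doing so when the syringe is opened and the fluid is pushed towards the ganglion. If serum and saline look different, whoever injects can see which one it is.

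This matters because several later steps depend on one person's blind. The main investigator conducts every follow-up interview, copies the scores into the database and classifies adverse events. The classification is a judgement, and it determines which patients count towards the primary safety endpoint. That endpoint is met if the event rate is not significantly greater with the serum, so a tendency to call fewer events related in that arm would make it easier to meet, and the opposite tendency harder. The primary efficacy outcome is a pain score, and a patient's answer can be coloured by an interviewer who knows the treatment.

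**Working it through.** The point rests on no figure of the plan, so the check sets the relevant statements side by side.

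1. **What is masked?** The syringes are said to look the same and to be sealed. The article does not say that the barrel is opaque, that the contents are covered, or that the two fluids match in appearance.

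2. **What is inside?** 3 mL of blood-derived serum or 3 mL of 0.9% saline. The article does not describe how either looks. That serum is coloured and saline clear is my assumption from general knowledge.

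3. **When does the seal stop helping?** At each injection. There are two per patient, so with 70 patients and one syringe per procedure there are up to 70 × 2 = 140 openings. The repeat is at 14 days and the first follow-up visit at 30 days, so both openings precede every follow-up score.

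4. **Who is present when it is opened?** The injection is described in the passive voice. An investigator withdraws the sample from the pharmacy that day. No sentence says that someone other than the main investigator operates. The syringe safeguard is directed at her by name of role, which has a purpose mainly if she is expected to see the syringes. This makes it likely, but not stated, that she injects.

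5. **What depends on her blind afterwards?**
   - Interviews: four per patient, so up to 70 × 4 = 280, all hers.
   - Efficacy scores: the patient answers and she transcribes.
   - Relatedness of adverse events: her determination.
   - Outcome analyses: her responsibility.

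6. **Which stated safeguards reach which step?**
   - The allocation list kept by laboratory and pharmacy protects the blind up to the injection, but not during it.
   - A blood draw in all patients protects the patient's blind, but not the operator's.
   - Self-completion protects the pain score in part. It does nothing for relatedness.
   - The monthly blinded audit can catch transcription errors. It is not described as reviewing relatedness, and it would not show that an interviewer knew the arm.

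7. **Scale.** With 35 patients per arm, moving one patient into or out of the related-event count changes that arm's proportion by 1/35 = 2.9 percentage points. This is a unit of measurement, not an estimate of bias. The article gives no event rate and no basis for saying how often a judgement would change.

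**The case against.** The strongest reply has four parts.

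- **Pain is rated by the patient.** This stands. A reader might infer that the main investigator is the only outcome assessor and that the syringes are the only safeguard. The documents do not support that: patients answer the questionnaires individually, the article presents this as an additional safeguard, and a blinded researcher audits the data. The efficacy outcomes are therefore partly protected. What remains is influence at the interview, and relatedness, which self-completion does not touch.

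- **The injector is not named.** This also stands. A reader might infer that the main investigator certainly handles the contents. The text says only that an investigator collects the sample, and other doctors of the unit take part at least in recruitment. Nor does it say that she decides relatedness alone, only that she determines it.

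- **The sentence may mean that filled syringes cannot be told apart.** It can be read so, since it refers to syringes with their samples. But it offers sameness and a seal as the reason, and a seal does not survive use. A reader might go further and conclude that allocation is revealed for every patient. That would require visibly different fluids and an uncovered barrel, and the article establishes neither.

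- **A condensed article leaves such detail to the full protocol.** This is fair for details that are merely omitted. Here the article states its mechanism and draws a conclusion from it, and the mechanism as stated does not carry the conclusion. If the full protocol already requires masking of the contents, one sentence saying so would settle that part.

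**Conclusion.** The concern holds in limited form. As described, the blinding of the main investigator covers the container and not the contents at injection, and the article does not separate the operator from the person who interviews patients and determines relatedness. She may therefore learn the arm before follow-up starts. This rests on two assumptions that the article neither confirms nor excludes: that she performs or closely attends the injection, and that serum and saline can be told apart in an uncovered syringe.

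The most exposed element is the relatedness judgement and, through it, the primary safety endpoint. Influence on patients at the interview comes second. The size and direction of any bias cannot be derived from the document. The case for acting is that the claim to be double-blind depends on this step and that securing it costs little.

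**What to change.** 1. Before release, the pharmacy covers every syringe, and any transparent line, with the same opaque sleeve in both arms. It already holds the allocation list and the samples, so this adds one step and some inexpensive material. The drawback is that the injected volume is slightly harder to see.

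2. Patients complete the questionnaires and seal them before the interview begins. This makes individual completion a fixed order of events at visits that already take place, and needs no extra staff.

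3. State both measures in the blinding section, in place of reliance on sameness and a seal.

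Sleeves help only injections still to come. Sealed questionnaires can be used at every remaining follow-up visit, including those of patients already treated, but they do not repair relatedness judgements for patients whose syringes were uncovered. The report should say from which patient onward the sleeves were used.
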